### Trial design

The study will be a cluster randomised controlled trial. Clusters are HIV treatment hospitals in Anambra state. Hospitals (the clusters) will be matched by type of hospital (e.g. secondary or tertiary) and the paired units will be randomly assigned to the intervention or the control arm. The trial has two periods – intervention period and post-intervention period. Each of these periods will run for a 1-year duration. Further details of the trial are shown in Tables 1 and 2 and Additional file 1. Figure 1 shows the schedule of enrolment, interventions and assessments for the trial design.

**Table 1 Tab1:** The World Health Organisation (WHO) trial registration dataset

Data category	Information
Primary registry and trial identifying number	The Pan African Clinical Trials Registry: https://pactr.samrc.ac.za/ (PACTR201806003040425)
Date of registration in primary registry	2 February 2018
Source of monetary or material support	European Developing Countries Clinical Trial Partnership (EDCTP)
Primary sponsor	Nnamdi Azikiwe University
Contact for public queries	[contact]
Public title	Conditional Economic Incentive and Motivational Interviewing to Improve Adolescents’ Retention and Adherence to Antiretroviral Therapy and Care in South East Nigeria: a Cluster Randomised Trial
Scientific title	Conditional Economic Incentive and Motivational Interviewing to Improve Adolescents’ Retention and Adherence to Antiretroviral Therapy and HIV Care in South East Nigeria: a Cluster Randomised Trial
Country of recruitment	Nigeria
Health condition or problem studies	HIV
Interventions	Conditional economic incentive and motivation interviewing
Key inclusion criteria	All patients with HIV who had transitioned from pediatric stage to a young person/adult; age 10–19 years irrespective of CD4+ cell count; currently off antiretroviral therapy (ART) despite multiple attempts to restart; willing to restart therapy and sign a patient agreement
Study type	Interventional
Date of first enrolment	Yet to commence
Target sample size	240
Recruitment status	Yet to commence
Primary outcome	HIV viral load
Key secondary outcome	CD4+ count, adherence to ART (measured using pill count) and adherence to appointment with hospital

**Table 2 Tab2:** Protocol for conditional economic incentives

Started ART	VL response and attended for MI	Voucher value (USD)
Week 12	VL < 20	5.6
6 months suppressed	Sustained VL < 20	2.8
9 months suppressed	Sustained VL < 20	2.8

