### Sample size

The sample size was calculated using a web-based sample size calculator of the UCSF Clinical and Translational Science Institute [17]. The sample size calculation is based on the proportion of patients with VL suppression ≤ 20 copies/mL – the main outcome measure. Based on a power of 80% and an α of 0.05 (two-sided), 63 patients per group will be needed to observe a 12% (assumed standard deviation of 24%) increase in the number of participants with VL suppression as previously reported [18]. After adjustment for the cluster design, based on the assumed intracluster correlation coefficient of 0.047 and a fixed cluster per arm of six HIV treatment hospitals, the effective sample size increased to 120 patients per arm (i.e. a total of 240 participants). Due to potential attrition that could arise as a result of severe adverse events, treatment failures or the participant simply deciding to withdraw, we added three participants per hospital increasing the number of participants in each arm to 138 (i.e. a total of 276 participants). A fixed number of six clusters or hospitals per arm (i.e. 12 hospitals in total for the trial) were informed by the fact that only 12 hospitals in Anambra State offer comprehensive HIV services including HIV-adherence counselling and antiretroviral treatment services and these 12 hospitals have appreciable HIV client load. Each of the hospitals will, therefore recruit 23 participants.

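### The cluster adjustment ignores that only 12 hospitals are randomised: on the protocol's own inputs an unadjusted 10-df comparison has about 72% power, not 80%

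*Protocol article*

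**What the plan says.** All inputs are in the Sample size section of the protocol article. The individually randomised step reads "Based on a power of 80% and an α of 0.05 (two-sided), 63 patients per group will be needed", and the target is "to observe a 12% (assumed standard deviation of 24%) increase in the number of participants with VL suppression". The cluster step reads "based on the assumed intracluster correlation coefficient of 0.047 and a fixed cluster per arm of six HIV treatment hospitals, the effective sample size increased", and the result is given as 120 per arm and 240 in total. Three more patients per hospital are added for attrition, giving 23 per hospital and 138 per arm. The section says that the number of hospitals is fixed because only 12 in the state offer comprehensive HIV services.

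On allocation, the Trial design section matches hospitals by type, and "the paired units will be randomly assigned to the intervention or the control arm"; Trial sites selection says the same. The Randomisation section instead describes allocation within two strata, secondary and tertiary. The Statistical analysis section and Table 3 name a chi-square or Fisher's exact test for the primary outcome.

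**The concern.** A design effect corrects the variance of the treatment comparison for clustering. It does not correct the reference distribution. The large-sample formula uses a critical value of 1.96, as if the between-hospital variance were known. Here six hospitals are compared with six, so that variance is estimated from 12 units. A cluster-respecting test that keeps the stated 5% level needs a larger critical value: 2.23 with 10 df, 2.26 with 9 df (two strata) or 2.57 with 5 df (six pairs). If 1.96 is kept with 10 df, the two-sided type I error is about 7.8%. The stated 80% power and two-sided 5% therefore do not both hold for an unadjusted cluster-level comparison at 120 per arm.

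Because 12 hospitals is a ceiling, the penalty is built into the design. A null result would be read as coming from a better-powered trial than was run. If the sponsor later corrected the SD but kept the same cluster step, the restated power would still be too high.

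**Working it through.** **Inputs (Sample size section).** Difference 12 points, SD 24, two-sided α 0.05, power 80%, ICC 0.047, six hospitals per arm.

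**1. Reproduce 63 per group.** n = 2(1.96 + 0.8416)²(24/12)² = 62.8, so 63. The t-based version gives 64, so the plan used the normal approximation.

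**2. Reproduce 120 per arm.** For a fixed number k of hospitals per arm, patients per hospital are m = n(1 − ICC)/(k − n·ICC) = 63 × 0.953/(6 − 63 × 0.047) = 19.76, so 20, and 6 × 20 = 120. Both figures reproduce exactly, which leaves no room for a small-cluster correction.

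**3. Standard error at 20 per hospital.** Design effect = 1 + 19 × 0.047 = 1.893. SE = 24 × √(2 × 1.893/120) = 4.263. Noncentrality = 12/4.263 = 2.815.

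**4. Power from that noncentrality, two-sided 5%.** At 23 per hospital (no attrition) the noncentrality is 2.912. The 9- and 5-df rows assume that hospital type explains none of the between-hospital variance.

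| Reference distribution | 20 per hospital | 23 per hospital |
|---|---|---|
| Normal | 80.4% | 83.0% |
| t, 10 df (unadjusted) | 71.8% | 74.7% |
| t, 9 df (two strata) | 70.8% | 73.7% |
| t, 5 df (six pairs) | 61.9% | 64.7% |

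A simulation of 200,000 trials using hospital means at 20 per hospital gave 72.0% (unpaired) and 62.1% (paired). The difference detectable with 80% power at 20 per hospital is 13.3 points with 10 df.

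**5. What a gain from matching or stratifying would do.** The between-hospital share of the variance of a hospital mean is 0.047/(0.047 + 0.953/20) = 0.497. Let hospital type explain a fraction R of the between-hospital variance. R is assumed, since the protocol gives no matching correlation. The variance of a hospital mean becomes 24²[0.047(1 − R) + 0.953/20], and SE = √(2 × variance/6). At R = 50% the variance is 40.98, SE is 3.696 and noncentrality is 3.247.

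| R (assumed) | 9 df | 5 df |
|---|---|---|
| 0% | 71% | 62% |
| 25% | 76% | 67% |
| 50% | 82% | 74% |
| 75% | 88% | 81% |

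**6. The same step on the proportion scale.** For a binary outcome the individual variance is p(1 − p). The protocol states no control suppression rate, so rates of 20-60% are assumed, with a 12-point gain and the same design effect. SE = √{[p₁(1 − p₁) + p₂(1 − p₂)] × 1.893/120}. At p₁ = 0.40 and p₂ = 0.52, SE = √[(0.2400 + 0.2496) × 1.893/120] = 0.0879 and noncentrality = 0.12/0.0879 = 1.365.

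| Control rate (assumed) | Normal | 10 df |
|---|---|---|
| 20% | 34% | 29% |
| 40% | 28% | 24% |
| 60% | 30% | 26% |

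On this scale the degrees-of-freedom step costs about 4 to 5 points. The much larger fall from the stated 80% comes from the SD.

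**The case against.** Five arguments can be made on the other side.

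- *The arithmetic is right.* A reader might infer that 63 or 120 was miscalculated. Neither was: 63, 120, 138 and 23 all follow from the inputs and the formula used. The defect is an approximation that fails with 12 clusters, and the power claim attached to 120 per arm fails with it.
- *The planned test is an individual-level chi-square or Fisher's exact test, so no t degrees of freedom apply.* It is true that the protocol names no cluster-level test, and that the size of the penalty depends on which cluster-respecting analysis is adopted. This does not rescue the 80%. The Sample size section itself adjusts for clustering, so its power claim presupposes an analysis that respects it.
- *Hospitals are paired, so power is 62%.* A reader might infer this from the Trial design section. The documents do not support it as a fixed figure. It assumes that matching by type gains nothing, and the Randomisation section describes strata, not pairs. The same caveat applies to the 71% with 9 df. If type explains enough of the between-hospital variance, an adjusted analysis could reach 80% on the stated inputs.
- *The corrected power is therefore 72%.* This is also tempting and also unsupported. It holds only with an SD of 24%, whereas √[p(1 − p)] is 40% at a rate of 20% and 50% at a rate of 50%.
- *Beside the SD problem this is a refinement.* In size, yes: 4 to 5 points on the proportion scale. It is a separate error, though, and correcting the SD alone would leave it in place.

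**Conclusion.** The point holds in a limited form. The cluster step omits any allowance for the small number of hospitals. On the stated inputs, an unadjusted cluster-level analysis with 10 df has power of 71.8%, against 80.4% from the plan's own formula, and using the whole attrition reserve raises it only to 74.7%. This is the one figure that follows from stated inputs without a further assumption about matching. For the stratified and paired analyses only a range can be given: from 71% and 62% with no gain from hospital type to 82% and 74% if type explained an assumed half of the between-hospital variance. All these figures accept the 24% SD. With binary variance and assumed control rates of 20-60%, 10-df power for a 12-point gain is about 24-29%. The error should be corrected together with the SD, since correcting either alone leaves power overstated.

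**What to change.** In the Sample size section, recompute power with a t reference distribution whose degrees of freedom match the randomisation and a cluster-respecting analysis: 10 if unadjusted, 9 with two strata, 5 if analysed as six pairs. First settle whether hospitals are paired or stratified, because the sections differ and the degrees of freedom follow from that choice. Do the calculation on the proportion scale, with a stated control suppression rate and variance p(1 − p). State any assumed gain from matching or stratification, preferably with the zero-gain figure beside it. Report the resulting power at 20 and at 23 per hospital, together with the difference detectable at 80% power. Do not replace 80% by 72% while keeping the 24% SD.

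The cost is one recalculation and a reworded paragraph, with no additional patients or hospitals. The drawback is a less favourable stated power.

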### Randomisation

We will stratify each cluster unit (HIV treatment hospital) according to the type of clinic (secondary or tertiary). We will randomly allocate each HIV treatment hospital in each stratum into the intervention arm or the control arm. The randomisation schedule will be done using Research Randomiser, a web-based computer random-number generator [19]. The randomisation schedule will be carried out by an independent person who is not part of the research team.

### Statistical analysis

Statistical analysis will be conducted using IBM SPSS for Windows, Version 20 (IBM Corp, Armonk, NY, USA). As shown in Table 3, descriptive statistics will be used to evaluate differences in demographic and clinical characteristics. Categorical variables will be expressed as frequencies or percentages and quantitative variables as means and standard deviations or medians and interquartile ranges. An intention-to-treat analysis will be conducted. A secondary per-protocol analysis will also be conducted. The latter will include only those participants who completed the treatment protocol originally allocated, providing results on the efficacy of the trial. If there is a significant difference between the intention-to-treat analysis and the per-protocol analysis, then the former will be reported. Comparison of dichotomous measurements between the intervention group and the control group will be conducted using the chi-square test (or Fisher’s exact test) while comparison of the mean of continuous measurements between the intervention group and the control group will be conducted using an independent *t* test. A two-sided *p* value of 0.05 will be used to indicate statistical significance.

**Table 3 Tab3:** Data analysis outline

Study objective	Outcome variable	Type of analysis
Objective 1: effectiveness of intervention	Primary outcome	
	HIV viral load	*χ*^2^ test or Fisher’s exact test
	Secondary outcomes	
	CD4+ count	Within group: paired-sample *t* tests or Wilcoxon signed-rank tests; between group – Student’s *t* test or Wilcoxon signed-rank tests
	Adherence to antiretroviral therapy (ART)	*χ*^2^ test or Fisher’s exact test
	Adherence to hospital appointment	Within group: paired-sample *t* tests or Wilcoxon signed-rank tests; between group – Student’s *t* test or Wilcoxon signed-rank tests
Objective 2: cost-effectiveness analysis	Cost-effectiveness of intervention	Incremental cost-effectiveness ratio
Objective 3: qualitative assessment of implementer’s perspective	Programme implementer’s perspective	In-depth interview (thematic content analysis)

Health resource implication and cost-effectiveness of the Incentive Scheme intervention will be assessed. Health resource use will be estimated from the health provider’s perspective, i.e. all cost incurred for providing the Incentive Scheme by a health service provider. Resource use items will include items such as staff time, consumables, cost of financial incentive and equipment. All patient and family resources will be excluded. An activity-based costing method will be used to measure resource use. Data-capture questionnaires will be developed and sent to all the study personnel in the different study sites to record all their activities or resource use. Resource use items will then be multiplied by unit costs to determine a cost item. The entire cost item will be summed up and divided by the number of participants to determine the cost of the incentive scheme intervention per patient. A cost-effectiveness analysis alongside the cluster randomised trial will be conducted to assess the cost per additional patient achieving viral suppression through the proposed intervention. Incremental cost-effectiveness ratio (ICER) of Incentive Scheme over usual care will be calculated to determine the cost-effectiveness of the former.

A in-depth interview (IDI) with all the health providers in the intervention arm will be conducted at the end of the study to assess their perspective on the programme’s feasibility. The IDI instrument to be used will be developed using the Pathfinder International Tool Series guideline on conducting IDI [20]. During the interview, notes and audio digital recording will be taken and non-verbal and gestural cues will also be observed. All recorded data will be transcribed verbatim into English by the researcher and research assistant independently. A thematic content approach, guided by the Graneheim and Lundman framework, will be utilised for qualitative data [21]. Responses from the IDIs will be read systematically through in order to indentify the meaning units. A meaning unit will be defined as a string of the text that expressed a single coherent thought, up to the point that the coherent thought changed [22]. The meaning units will be coded using a describing cue related to the content of the meaning unit. Codes concerning the same subject will be grouped together into categories. The interview guide will be used as a point of departure for grouping information, deductively. Information obtained during the IDIs will be analysed and merged according to the codes and themes. Original data will be reassessed after analysis in order to detect any concepts or information that may be missed.

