### Intervention

A structured adherence support scheme termed the ‘Incentive Scheme’ will be applied to the intervention hospitals while the control hospitals will receive usual care. The Incentive Scheme added to the usual care involves financial incentives linked to viral load (VL) combined with attendance for motivational interviewing (MI) with an adherence counsellor trained in MI techniques. (Table 2) [14]. Training on MI will be in accordance with an MI guide that covers key points for MI as well as examples and key insights to assessing patient risk, risk reduction counselling and inspiring behaviour change [16]. Participants in hospitals randomised to usual care will receive the normal care obtainable in the HIV treatment hospitals. This typically involves monthly or bi-monthly scheduled hospital visit for medical examination, prescription refill and adherence counselling, bi-yearly VL assessment, and yearly CD4^+^ count analysis.

In addition to the usual care, participants in the intervention hospitals will receive MI at baseline and following initiation of ART, they will receive a gift voucher of US$5.6 when VL < 20 copies/mL at 12 weeks, a gift voucher of US$2.8 if the VL remains suppressed for the next 3 months, and the next 6 months, and finally a gift voucher of US$5.6 if the VL remains < 50 copies/mL at 1 year. All incentives will be conditional not only on patients meeting their VL target but attending for MI. Those with VL higher than the thresholds will not receive the incentive. The potential maximum cumulative financial incentive is US$16.8 if viral suppression is sustained for 12 months. The patient will have the liberty to withdraw from the scheme at any time point. Routine hospital data will be collected and outcomes will be assessed by changes in HIV VL and CD4+ count from baseline, at 12 months from enrolment and at 24 months to establish whether any benefit is seen from the intervention could be sustained when financial incentives cease. Each patient in the study will be assigned to a study nurse working in the HIV treatment hospital and they will be tracked with their mobile phone numbers.

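### The primary test of viral suppression uses neither the measured baseline viral load nor the hospital type used in randomisation; adjustment within a hospital-level analysis would help, by an amount that depends on a correlation the protocol does not give

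*Protocol article*

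**What the plan says.** The Statistical analysis section of the protocol article fixes the method: "Comparison of dichotomous measurements between the intervention group and the control group will be conducted using the chi-square test (or Fisher’s exact test". Table 3 repeats it for the primary outcome. Neither place names a covariate, stratum, pair or hospital term, and baseline characteristics are only described.

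Elsewhere the article gives two variables that such a test cannot use:

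- **Baseline viral load.** The Intervention section says "outcomes will be assessed by changes in HIV VL and CD4+ count from baseline, at 12 months from enrolment and at 24 months", so a baseline value is taken.
- **The randomisation factor.** The Randomisation section says "We will stratify each cluster unit (HIV treatment hospital) according to the type of clinic (secondary or tertiary". Trial design and Trial sites selection describe the hospitals as matched by type, with the members of each pair allocated to opposite arms.

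No reason is given for leaving either out of the primary comparison.

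**The concern.** This is a stated choice and not a detail left to a later plan, because a two-group chi-square or Fisher test cannot carry a covariate.

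Two things are at stake. Baseline viral load is the collected variable closest to the outcome. If it predicts later suppression, leaving it out leaves avoidable variance in the estimate, and with six hospitals per arm a chance difference at baseline goes uncorrected. Hospital type is balanced by the allocation. If it is prognostic and then omitted, a hospital-level standard error still contains the variance that the design removed, and the benefit of stratifying is lost.

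The issue is separate from clustering: an analysis that handled hospitals correctly but stayed unadjusted would lose the same information.

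**Working it through.** **Inputs from the Sample size section.** "Based on a power of 80% and an α of 0.05 (two-sided), 63 patients per group will be needed"; the target is to "observe a 12% (assumed standard deviation of 24%) increase in the number of participants with VL suppression as previously reported"; clustering is "based on the assumed intracluster correlation coefficient of 0.047 and a fixed cluster per arm of six HIV treatment hospitals"; and "the effective sample size increased to 120 patients per arm (i.e. a total of 240 participants". That is 20 analysed patients per hospital. The documents give no baseline-to-outcome correlation (rho) and no control-arm suppression rate.

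**1. Reproduce the plan.**
- Before clustering: n = 2 × (1.96 + 0.842)² × 24² / 12² = 62.8, so 63 per group.
- Per hospital: 63 × (1 − 0.047) / (6 − 63 × 0.047) = 19.76, so 20, giving 6 × 20 = 120 per arm.
- Design effect: 1 + 19 × 0.047 = 1.893.
- Variance of the difference: 2 × 24² × 1.893 / 120 = 18.17, so the standard error is 4.263 points.
- Power: Φ(12/4.263 − 1.96) = 80.4%. A hospital-level t test on 10 df gives 71.8%.

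Both 63 and 120 reproduce. The 80% therefore belongs to a cluster-respecting, unadjusted analysis.

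**2. Adjust for baseline viral load (rho assumed).** If baseline explains variance between and within hospitals alike, multiply the variance by 1 − rho². If it acts only within hospitals, only that part shrinks. The variance of a hospital mean is proportional to 0.047 + 0.953/20 = 0.09465, of which 49.7% is between hospitals. The multiplier is then [0.047 + (1 − rho²) × 0.04765] / 0.09465. Entries are power, with the gain over 80.4% (normal) or 71.8% (t) in brackets. The t columns use 9 df, one being spent on hospital type.

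| rho | Both levels, normal | Both levels, t | Within only, normal | Within only, t |
|---|---|---|---|---|
| 0.2 | 81.9% (+1.6) | 72.5% (+0.7) | 81.2% (+0.8) | 71.6% (−0.2) |
| 0.3 | 83.9% (+3.5) | 74.8% (+2.9) | 82.2% (+1.8) | 72.7% (+0.9) |
| 0.4 | 86.7% (+6.3) | 78.0% (+6.2) | 83.5% (+3.2) | 74.3% (+2.5) |
| 0.5 | 90.2% (+9.8) | 82.4% (+10.6) | 85.3% (+5.0) | 76.4% (+4.6) |

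The plan's SD of 24% fits a yes/no outcome only near a rate of 6% or 94%. With binomial SDs and an assumed control rate of 20% to 60%, rho = 0.5 at both levels adds about 6 to 9 points from a much lower start. At a 40% control rate, for example, power goes from about 28% to 35% (normal).

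**3. Hospital type (assumed to explain half of the between-hospital variance and to be balanced by the allocation).** The true variance falls to (0.0235 + 0.04765) / 0.09465 = 0.752 of what an unadjusted hospital-level test estimates. Its two-sided size is 2 × [1 − Φ(1.96/√0.752)] = 2.4%. Scaling the 10-df critical value instead (2.228/√0.752 = 2.57) gives about 2.8%.

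**4. Chance imbalance.** If baseline viral load has the same ICC (assumed), the arm difference in its mean has a standard error of √(2 × 1.893 / 120) = 0.178 SD. At rho = 0.5, a one-standard-error imbalance moves the estimate by 0.5 × 24 × 0.178 = 2.1 points with the plan's SD. With a binomial SD at 40% suppression (49 points) it moves by 4.4 points.

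**5. The test as written.** Ignoring a design effect of 1.893, its type I error is 2 × [1 − Φ(1.96/√1.893)] = 15.4% at 20 per hospital, or 16.9% at the recruited 23. Under the plan's effect it rejects about 92% of the time.

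**The case against.** A reader might infer that the planned test gives up 10 points of power. The documents do not support that, for three reasons.

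- The chi-square test ignores clustering, so it rejects too often. Replacing it with the adjusted hospital-level test lowers the rejection rate from about 92% to about 82% even at rho = 0.5. The gain exists only against a cluster-respecting unadjusted analysis. This stands, and it makes clustering the larger fault of the test.
- Nothing in the article supports rho = 0.5. Eligibility requires participants to be off treatment, so suppression at baseline will hardly vary, and only the level of viral load could predict the result 12 or 24 months later. This stands in part. The level may still vary, since the assay quantifies from 20 to 10⁷ copies/mL, but how well it predicts is unknown.
- Ten points also needs baseline to explain between-hospital variance as well as within-hospital variance. Otherwise the gain is about half. This stands.

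A reader might also take chance imbalance for a further bias on top of the lost power. It is not: a valid hospital-level standard error already contains it, so step 4 describes the same variance as step 2. Nor does hospital type add to the imbalance concern, because the allocation largely balances it. The 2.4% to 2.8% describes a hospital-level test that the plan does not contain, and the share of variance due to type is assumed.

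What the objections leave untouched is that the article fixes a test unable to use two variables already in hand, and gives no reason.

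**Conclusion.** The point holds in a limited form. The stated primary comparison omits baseline viral load and the randomisation factor, and a cluster-respecting analysis that included them would generally be more precise.

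Under the plan's inputs and a normal approximation, the gain from baseline viral load runs from about 2 points at rho = 0.2 to 10 at rho = 0.5, and about half of that if it acts within hospitals only. With the t test it can be nil at rho = 0.2. These figures rest on an assumed rho and on the plan's SD of 24%, which is doubtful for a proportion. The benefit from hospital type rests on an assumed share of variance.

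This is a worthwhile improvement in efficiency and in consistency with the design. It does not by itself invalidate a comparison that handles clustering properly, and it cannot rescue one that does not.

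**What to change.** In the Statistical analysis section and Table 3, specify as primary, at both 12 and 24 months, a comparison of hospitals adjusted for baseline log10 viral load and the randomisation factor (hospital type, or the pair if pairs are what is randomised). One form that is feasible in the planned software:

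1. Fit a logistic regression of suppression on baseline log10 viral load and hospital type, leaving out arm.
2. For each hospital, take the observed minus the expected proportion suppressed.
3. Compare the 12 hospital values between arms with a t test on 9 df (12 hospitals, less 2 for the arms and 1 for type).

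Keep the unadjusted proportions by arm as a descriptive summary.

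The cost is wording only, since both variables are collected or known. Adjusting for type spends one degree of freedom, about 1 point of power if neither covariate is prognostic (71.8% on 10 df against 70.8% on 9 df). Using pairs as the factor costs more. A simple rule for a missing baseline viral load is also needed, such as a missing indicator or single imputation.

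### The primary test treats adolescents as independent although 12 hospitals are randomised; at the protocol's own ICC of 0.047 its two-sided error is about 15–17% (chi-square) or 12–15% (Fisher), not 5%

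*Protocol article*

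**What the plan says.** The Protocol article randomises hospitals. Trial design says that hospitals are matched by type and "the paired units will be randomly assigned to the intervention or the control arm"; Trial sites selection says the same. Randomisation describes strata of secondary and tertiary clinics: "We will randomly allocate each HIV treatment hospital in each stratum into the intervention arm or the control arm". Study objectives states that the main outcome is measured on the individual adolescent.

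Sample size allows for this structure. It begins with "Based on a power of 80% and an α of 0.05 (two-sided), 63 patients per group will be needed" and then inflates: "After adjustment for the cluster design, based on the assumed intracluster correlation coefficient of 0.047", with six hospitals per arm. This gives 120 per arm, and 138 after the attrition allowance, or 23 per hospital.

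Statistical analysis then names the tests: "Comparison of dichotomous measurements between the intervention group and the control group will be conducted using the chi-square test", or Fisher's exact test, with an independent t test for continuous measurements. Table 3 lists the chi-square or Fisher test for the primary outcome. The threshold is nominal: "A two-sided *p* value of 0.05 will be used to indicate statistical significance". Neither the text nor Table 3 mentions a hospital effect, a hospital-level summary, a design-effect correction, or a term for hospital type or pair.

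**The concern.** Adolescents attending one hospital share staff, supply and catchment, so their outcomes are correlated. The protocol accepts this when it sets the sample size and then drops it when it sets the test. Chi-square, Fisher and the independent t test all take the 240 to 276 participants as independent, whereas only 12 units are allocated at random. Chance differences between hospitals then count as evidence of an intervention effect, and the nominal 5% threshold is crossed too often when there is no effect. This concerns the primary efficacy claim. The between-group tests of CD4+ count, pill-count adherence and appointment adherence have the same flaw.

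**Working it through.** **Inputs, all from Sample size unless noted.** Two-sided α 0.05; power 80%; difference 12 points with SD 24 points; ICC ρ = 0.047; k = 6 hospitals per arm; m = 20 per hospital before and 23 after the attrition allowance. The test is from Statistical analysis and Table 3.

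**1. Reproduce the plan's figures.**
- Individually randomised: n = 2 × (1.960 + 0.842)² × (24/12)² = 62.8, so 63 per group.
- Fixed number of clusters: m = n(1 − ρ)/(k − nρ) = 63 × 0.953/(6 − 63 × 0.047) = 60.04/3.039 = 19.76, so 20 per hospital and 120 per arm.
- Attrition: 20 + 3 = 23 per hospital, 138 per arm.

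All three stated figures reproduce, so the ICC of 0.047 is in active use in the design.

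**2. Error of the unadjusted chi-square test.** Design effect DE = 1 + (m − 1)ρ. True two-sided size = 2 × [1 − Φ(1.96/√DE)].

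| m | DE | √DE | 1.96/√DE | true size |
|---|---|---|---|---|
| 20 | 1 + 19 × 0.047 = 1.893 | 1.376 | 1.425 | 15.4% |
| 23 | 1 + 22 × 0.047 = 2.034 | 1.426 | 1.374 | 16.9% |

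The √DE column is the factor by which the standard error is too small: about 1.4.

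**3. Simulation check.** Twelve hospitals, beta-binomial outcomes, ICC 0.047, null suppression proportions 0.3, 0.5 and 0.6 (assumed; 40,000 runs, 10,000 for Fisher):

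| test | m = 20 | m = 23 |
|---|---|---|
| chi-square | 15.0–15.9% | 16.4–17.2% |
| Fisher's exact | 12.1–13.3% | 14.1–14.5% |
| t test on the 12 hospital proportions | 4.8–5.2% | 4.8–5.0% |

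The hospital-level test keeps the stated 5%, so the excess comes from the choice of test.

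**4. Sensitivity of the chi-square size.**
- ICC 0.01: DE 1.19 to 1.22, size 7.2–7.6%.
- ICC 0.10: DE 2.90 to 3.20, size 25–27%.
- ICC 0.047, with hospital type balanced between arms and explaining a share f of the between-hospital variance: the variance factor becomes (1 − ρ) + mρ(1 − f). For f = 0.25 it is 1.658 (m = 20) or 1.764 (m = 23), size about 13–14%. For f = 0.5 it is 1.423 or 1.494, size about 10–11%. The protocol gives no value of f; these are illustrations.

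**5. Power of a valid hospital-level test on the plan's 12/24 inputs.** SE = 0.24 × √(2DE/6m) = 0.0426 (m = 20) or 0.0412 (m = 23); non-centrality = 0.12/SE = 2.81 or 2.91.

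| analysis | df | critical t | power, m = 20 | power, m = 23 |
|---|---|---|---|---|
| two arms, no strata | 10 | 2.228 | 72% | 75% |
| two strata | 9 | 2.262 | 71% | 74% |
| six matched pairs | 5 | 2.571 | 62% | 65% |

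These rows give no credit for variance removed by strata or pairs. They also take the 12/24 inputs at face value; whether an SD of 24 points suits a yes/no outcome is a separate question.

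**The case against.** The best defence is that this is a condensed article, that Table 3 is only an outline, and that a separate analysis plan may exist. That would answer silence. Here the article names the primary test twice, and that test contradicts the article's own sample size section. The defence does not stand.

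Several stronger readings are tempting and are not supported:

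- *That 15–17% is the real error rate of the planned analysis.* It applies to chi-square only; Fisher is lower. Both figures rest on an ICC that the protocol labels as assumed, and balance on hospital type could lower them.
- *That no positive result could be believed.* Too strong. With 9 or 10 df, an unadjusted z of about 3.1 to 3.2 (critical t × √DE, for example 2.262 × 1.376 = 3.11), or p of roughly 0.001 to 0.002, would on average still pass a correct 5% test. The doubt falls on moderately significant results.
- *That reported confidence intervals would be too narrow.* The article plans p values and mentions no intervals, so the consequence belongs to p values and standard errors.
- *That pairing versus stratification is an equally serious contradiction that forces 5 df or 9 df.* Both descriptions use one factor, hospital type. Pairs formed on type alone add nothing beyond the stratum, so a stratified analysis can be defended under either wording. The texts need reconciling, but as a clarification.

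**Conclusion.** The concern holds and should be corrected before analysis. The stated primary test does not respect the unit of randomisation and conflicts with the protocol's own allowance for clustering. At the assumed ICC of 0.047 the stated 5% error is about tripled for chi-square and more than doubled for Fisher. At an ICC as low as 0.01 the chi-square inflation is modest; even if hospital type explained half of the between-hospital variance at 0.047, chi-square would still be at about 10–11%. The result assumes equal hospital sizes of 20 to 23 and a common ICC in both arms.

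**What to change.** In Statistical analysis and Table 3, replace the between-group tests for the primary and secondary outcomes with one of:

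- a t test on hospital-level summaries (for the primary outcome, the 12 suppression proportions), accounting for hospital type. This has 9 df if there are exactly two strata, each represented in both arms; the protocol does not say how many hospitals are of each type.
- a mixed model (logistic for binary outcomes) with a hospital random intercept, hospital type as a fixed effect and small-sample degrees of freedom.

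As a secondary step, make Trial design, Trial sites selection and Randomisation describe one scheme, matched pairs or strata, and let the analysis follow the scheme actually used.

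**Cost.** No new data, since hospital and hospital type are known for every participant. Uncertainty becomes wider. Sample size should restate the power: on its own inputs about 71–75% for a hospital-level test, or about 62–65% for a paired analysis on 5 df, in place of 80%.
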